#### Statistical analysis

All analyses will be fully specified in a comprehensive Statistical Analysis Plan and agreed by the Steering Committee. Analyses will be carried out in accordance with relevant guidance, including Reporting of studies Conducted using Observational Routinely-collected Data (RECORD)^15^ and Strengthening the Reporting of Observational Studies in Epidemiology (STROBE).^16^

We will include at least 14 maternity units offering only in-hospital cervical ripening and 12 offering dinoprostone home cervical ripening (~95 000 deliveries per annum). We will invite additional maternity units to opt in to data provision, to allow contingency in case of ‘cross overs’ due to sites changing their IOL protocols during the study period.

We considered a superiority design for CHOICE, but decided against it because (a) safety is a key concern to both clinicians and women, and was specified as the important outcome in the commissioning brief; (b) it is not plausible to hypothesise that home cervical ripening (intervention) is safer than in-hospital cervical ripening (comparator—the standard of care) and (c) it is not ethical to use a superiority design to test an intervention, which may be worse (in terms of safety) than the established standard. Therefore, a non-inferiority design was chosen with a non-inferiority margin of 4% (deemed as likely to be an important difference on consultation with women and clinicians) for the primary outcome of NNU admission.

Establishing the appropriate non-inferiority margin was complicated by recognition that the dimensions that are hypothesised to show benefit, that is, acceptability to women and partners, and a reduction in costs appeal to different audiences—women will be primarily interested in acceptability and largely indifferent to costs (in a free at point of care NHS), whereas the potential reduction in costs will likely be the primary focus for the healthcare provider. We were also conscious that due to the inflation of the sample size due to (a) clustering, (b) losses due to non-matching in the propensity analysis and (c) loss to follow-up, the sample size for a smaller non-inferiority margin would quickly become not feasible within a realistic budget and timeframe. Given that, regardless of a superiority or non-inferiority design, any specific sample size will estimate the treatment effect to a certain level of precision (eg, the width of a 95% CI), we are confident that our final comparison group of 1920 in each arm (with ~115 NNU admissions in each arm (see sample size calculation below)), we will generate sufficient high-quality evidence to definitively answer the questions around safety, effectiveness, acceptability and cost-effectiveness for this important question

For the principal analysis of the primary outcome, we will use mixed effects logistic regression for the non-inferiority comparison of NNU admission within 48 hours of birth for 48 hours or longer (Yes/No). As sensitivity analyses to demonstrate that the estimated treatment effects are robust to the chosen method, we will also explore propensity score weighting (by inverse probability of receiving specified treatment) and single-stage regression, without using any propensity scoring, adjusting directly for the baseline factors relevant for treatment indication. We will also use propensity score matched (PSM) adjustment to control for treatment indication bias. The logistic model underlying the PSM will include variables such as age, Bishop’s score, previous vaginal birth, c-morbidities and relevant hospital-level factors, with 1:1 matching. Potential confounding variables will be identified before the start of the analysis, and these will be finalised after exploration of the data at the pilot stage, through the creation of directed acyclical graphs.

Similar analyses will be used for analyses of secondary outcomes, using logistic, linear, negative binomial and time-to-event regressions. For example, we will analyse the duration of hospital stay during IOL, time spent at home, total hospital stay and time to birth using linear models; while birth outwith hospital and breastfeeding will be analysed using logistic regression; and mode of birth using multinomial logistic regression.

For the remaining maternal secondary outcomes, we will include hyperstimulation, ≥1 induction agent, oxytocin use for induction or augmentation, maternal ICU/High dependency unit admission, haemorrhage, uterine rupture, pulmonary embolus and cardiorespiratory arrest. For the neonatal secondary outcomes, we will include meconium aspiration syndrome, respiratory support, neonatal infection, umbilical cord prolapse, neonatal birth trauma, neonatal encephalopathy (Grade II/III), therapeutic hypothermia and neonatal death. Logistic regression and Poisson or negative binomial regression, possibly inflated for excess zeros will be used as appropriate. For outcomes with a small number of events, we will use the appropriate exact regression procedure. As per the primary outcome, we will assess the influence of missing data for secondary outcomes using appropriate sensitivity-type analyses. We recognise that there are many secondary outcomes being analysed, as per the recommended core outcome set.^17^ We do not propose to make any formal statistical adjustment for the multiple comparisons. However, a caveat will be clearly expressed regarding the possibility of type 1 statistical error, given the multiple comparisons made. We will consider the following subgroup analyses, based on sufficient numbers to allow meaningful analyses: (a) nulliparous and parous women; (b) indication for IOL (post-dates IOL; maternal or clinician preference; maternal age and discomfort or social indication).

We propose the following sensitivity analyses: (a) within-site comparison of home versus in-hospital cervical ripening (restricted to sites that offer home cervical ripening), (b) per protocol analysis (women who actually are discharged home after commencing cervical ripening) and (c) complete case analysis to assess the effect of any strategies to deal with missing data.

Data from the larger cohort of women having IOL at 37+^0^ weeks’ gestation or more will be used to contextualise our findings on the background of unit practices and populations undergoing IOL. There is considerable inter-unit variation in both the rates of IOL and the risk profile of women giving birth, that needs to be considered. It will also allow us to capture any changes in practice over the study period regarding criteria for eligibility for home cervical ripening and change in method of IOL. This will help ensure the generalisability of our findings.

Future long-term outcome evaluation will be possible through data linkage to Hospital Episode Statistics and Scottish Morbidity Records.

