#### Sample size

The sample size is based on our principal analysis (women with singleton pregnancies having IOL at 39 weeks’ gestation or more) and primary comparison (home cervical ripening vs in-hospital cervical ripening with dinoprostone), estimated 6% NNU admission rate^1^ for babies born to mothers having IOL at >39 weeks’ gestation with no more than 4% excess NNU admission rate (from 6%), at 90% power, 2.5% one-sided alpha and an estimated ICC of 0.01. We will require 160 women in each of 12 sites (clusters) with uncomplicated pregnancies at 39 weeks or more undergoing IOL (total 1920 in each arm). To account for the fact that (a) only around 50% of women eligible for home cervical ripening in the intervention arm will actually initiate home cervical ripening, and (b) a larger pool of women is required in the control arm to allow for propensity score matching, our required sample size is 1920×2 (number of arms)/0.5 (numbers of women actually starting home cervical ripening and matching)/0.9 (for missing data), giving an overall required sample size of 8533.

Based on an estimate that 22% of all maternities have IOL at 39 weeks or more^1^ and that ~29% of these would be eligible for participation in our principal analysis (from scoping data from potential participating sites), and, in home cervical ripening sites ~50% of these will take up home cervical ripening, we anticipate achieving our recruitment targets within 20 months.

Current data from the National Maternity and Perinatal Audit (NMPA) for 2019 suggests that the national average rate of IOL after 37 weeks is 29.6%.^1^ As our proposed participating units have about 90 000 births per annum, we anticipate collecting data on approximately 41 000 women having IOL at 37 weeks’ gestation or more.

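### The inverse-probability weighting offered as a check of method targets a different population from the 1:1 matching it is meant to check, so modest gaps between the two may not be a matter of method

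*Protocol article*

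**What the plan says.** The Statistical analysis section of the protocol article names mixed effects logistic regression as the principal analysis of the primary outcome and adds propensity score matched adjustment, with 1:1 matching, to control treatment indication bias. The Abstract pairs the two as the approach to the primary comparison. The Sample size section is built on a matched group of 1920 women per arm. It explains its inflation by saying that "only around 50% of women eligible for home cervical ripening in the intervention arm will actually initiate home cervical ripening" and that "a larger pool of women is required in the control arm to allow for propensity score matching".

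The alternative methods are introduced in these words: "As sensitivity analyses to demonstrate that the estimated treatment effects are robust to the chosen method". The first of them is described thus: "we will also explore propensity score weighting (by inverse probability of receiving specified treatment"). The second is a single-stage regression that adjusts directly for baseline factors.

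Under Exposure and outcomes, the exposure group is women who plan home ripening, and the comparator group comes only from units that do not offer it. The margin is an absolute one: "no more than 4% excess NNU admission rate (from 6%), at 90% power, 2.5% one-sided alpha and an estimated ICC of 0.01".

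**The concern.** Matching each home woman to one comparator from a larger pool keeps the home women and selects comparators who resemble them. The result is the effect in women who plan home ripening, or in those of them who find a match. Weighting each woman by the inverse probability of the treatment she received makes both groups resemble the whole pooled cohort. The result is the effect in home women and women at in-hospital-only units together.

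These are two target populations. The model is logistic and the margin is a risk difference, so even a constant odds ratio gives different risk differences where baseline risk differs. A gap between the matched and the weighted result would then mix a change of population with any difference due to method. A check meant to isolate method should hold the population fixed.

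**Working it through.** **The plan's own figures.** Inputs from the Sample size section are 6% in both arms, margin 4 points, one-sided alpha 2.5%, power 90%, ICC 0.01, and 12 clusters of 160 per arm.
- Per arm without clustering: (1.960 + 1.282)² × 2 × 0.06 × 0.94 / 0.04² = 741.
- Design effect: 1 + 159 × 0.01 = 2.59. Then 741 × 2.59 = 1919, against 1920 stated.
- Total: 1920 × 2 / 0.5 / 0.9 = 8533, as stated.

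The sample size reproduces, and it assumes equal true rates in the two arms.

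**Size of the comparator pool.** Removing the allowance for missing data leaves 8533 × 0.9 / 2 ≈ 3840 per arm. In the home arm half take up home ripening (1920). In the comparator arm all 3840 are available for matching. Home women are therefore 1920 / 5760 = 1/3 of the pooled cohort.

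**Relation between the two targets.** Weighted effect = (1/3) × effect in home women + (2/3) × effect in the comparator pool.

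**Pass limit.** SE = √(2 × 0.06 × 0.94 × 2.59 / 1920) = 1.23 points, so the half-width is 1.96 × 1.23 = 2.42 points. An estimate passes if it is below 4 − 2.42 = 1.58 points. This SE is used below for both methods, which is a simplification.

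**Illustration.** These assumptions are not in the documents: half of the comparator pool resembles home women and half resembles women who would not take up home ripening; their baseline risks average 6%; the odds ratio is constant at (0.10/0.90)/(0.06/0.94) = 1.741. For baseline risk p, RD(p) = OR × odds/(1 + OR × odds) − p. Matched = RD(takers). Weighted = [2 × RD(takers) + RD(decliners)]/3.

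| Baseline risk, takers / decliners | Matched (points) | Weighted (points) | Gap (points) | Gap / SE |
|---|---|---|---|---|
| 6% / 6% | 4.00 | 4.00 | 0 | 0 |
| 5% / 7% | 3.39 | 3.79 | 0.40 | 0.32 |
| 4.5% / 7.5% | 3.08 | 3.68 | 0.60 | 0.48 |
| 4% / 8% | 2.76 | 3.56 | 0.80 | 0.64 |

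With an odds ratio of 1 the gap is zero in every row.

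**Does it change the reading?** Not in these rows. The matched estimates already have upper limits of 5.18 to 5.81 points (2.76 + 2.42 to 3.39 + 2.42), so both methods fail the margin. Near the pass limit it can. With 4%/8% and an odds ratio of 1.4, matched is 1.51 (upper limit 3.93, passes) and weighted is 1.96 (upper limit 4.38, fails). For a matched estimate of 1.5 points, the gap is about 0.18 points (0.15 SE) at 5%/7% and 0.44 points (0.36 SE) at 4%/8%.

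**The case against.** The strongest reply is that this belongs in the analysis plan. The article says all analyses will be fully specified there, and it only undertakes to explore weighting. That would dispose of a complaint about missing detail. Here, however, the article itself names the type of weight and states what the check is for, and the two do not fit. If the analysis plan already weights to the home group, only the article's wording is at fault.

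Several stronger readings are tempting, and the documents do not support them:
- *That the principal effect is defined as the effect in home women.* No target population is stated. The Statistical analysis section mentions matching only after the sensitivity analyses. That matching belongs to the primary approach is the natural reading of that section with the Abstract and the Sample size section, but it is an inference.
- *That the weights target all eligible women.* Women at home-offering units who do not plan home ripening are outside the primary comparison. The weighted target is home women plus women at in-hospital-only units.
- *That the documents show home women to be at lower risk than the comparators.* The statement under Exposure and outcomes compares women within units offering both settings. The primary cohort is also restricted to uncomplicated pregnancies. The risk difference between home women and this comparator pool is not given, so the splits above are assumptions.
- *That the mismatch would commonly reverse the non-inferiority conclusion.* Under the design's own assumption of equal rates, the gap is zero.

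It is also fair to say that weighting is a sensitivity analysis and does not decide non-inferiority, and that the pooled-cohort effect is a legitimate question for a service considering home ripening. Both points stand. They argue for labelling that result correctly.

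**Conclusion.** The point holds as a modest mismatch in a sensitivity analysis. On the natural reading, matching estimates the effect in matched women who plan home ripening, while the weights as worded estimate it in a pooled cohort that is about two thirds comparators. The two risk differences can differ without any failure of method if baseline risks differ and the effect is not null.

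Under the splits worked through, the gap is 0 to about 0.8 points, or up to 0.64 of the design SE. It matters for the 4-point margin only when the estimate lies near 1.6 points. This rests on the assumed baseline risks, a constant odds ratio, a comparator pool twice the size of the home group, and one SE for both methods. The sample size is unaffected.

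**What to change.** In the Statistical analysis section, and in the analysis plan if it has the same wording:
- For the weighting presented as a check of method, use weights that target the home group: 1 for home women and ps/(1-ps) for comparators.
- Standardise the direct-adjustment regression over the home women, so that all three methods estimate one risk difference against the same margin.
- If the inverse-probability result is kept, report it as the effect in the pooled cohort. Treat it as a separate question and not as evidence of robustness to method.

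One limit remains. If some home women go unmatched, the matched effect covers only those matched, while the new weights cover all home women; reporting the number unmatched lets a reader judge this.

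The cost is one line of wording and slightly more analysis. No new data are needed, and 1920 per arm and 8533 overall stand.

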#### Exposure and outcomes

Our primary aim is to compare home versus in-hospital cervical ripening. We will collect data at individual level. The exposure group will be women who, at the start of the cervical ripening process, plan to have home cervical ripening. The comparator group will be women who planned to have in-hospital cervical ripening from maternity units not offering home cervical ripening. This will minimise potential bias arising from the fact that, in maternity units which offer both home and in-hospital cervical ripening, the risk of complications in the babies of women having home cervical ripening (lower risk pregnancies) is inherently different to that of babies of women having in-hospital cervical ripening (higher risk pregnancies).

As the NICE recommended agent for cervical ripening is vaginal prostaglandin, our primary comparison will be home dinoprostone versus in-hospital dinoprostone. Dinoprostone is now most commonly administered as 10-mg slow-release pessary (Propess, Ferring), which stays in place for 24 hours. We will use this formulation in our primary comparison.

We will include a secondary exploratory comparison—home cervical ripening with balloon catheter (exposure) versus home cervical ripening with dinoprostone (comparator), to explore if there are any indications of different safety profiles of these two methods of home cervical ripening.

Our proposed primary outcome will be admission to an NNU/special care baby unit for 48 hours or longer, initiated within 48 hours of birth. NNU admission is a marker of neonatal morbidity and is the leading core outcome defined for studies of IOL.^14^ Any increase in NNU admission of term babies is undesirable due to the separation of mother and baby. However, NNU admission rates are highly variable between maternity units and are likely to depend on local policies and culture. We, therefore, plan to use a primary outcome, which represents more severe neonatal morbidity (admission to a NNU within 48 hours of birth for 48 hours or longer), which is less likely to be influenced by site-specific factors. We may re-define the parameters of NNU admission used in the primary outcome after analysis of pilot data (see section ‘Pilot phase’).

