The Labour Agentry Scale (LAS; short form)^22^: the LAS is a well-established, validated measure of women’s experience during labour and birth. The short-form LAS includes 10 items with a 7-point Likert-type response. It measures perceived control during labour, which is the woman’s sense of mastery over internal and environmental factors and is highly correlated with satisfaction with care. The LAS will be the primary outcome.A modified version of the IOL satisfaction questionnaire^23^ tested in the Balloon Catheter Versus Propess for Labour Induction (PROBIT-F) trial.^24^ This questionnaire focuses specifically on women’s experiences of aspects of IOL, including information, anxiety and physical and emotional discomfort.The short-form Warwick-Edinburgh Mental Well-Being Scale (WEMWBS)^25^: a seven-item scale that measures mental well-being (as opposed to mental illness or disorder) representing positive attributes of well-being, including feeling and functioning.Additional questions, which will inform the economic analysis from the woman’s perspective, will cover resource use and expenditures of cervical ripening for women, including number of returns and phone calls to hospital, time distance, mode of travel to and from hospital, partner role, additional expenditure on maternity items and medication while at home, and additional childcare expenditure (if any) while at home.The survey will include demographic questions, questions about the process of IOL, questions relating to the impact of COVID-19 19 on their experience of IOL, a question asking women if they would be willing to be contacted regarding possible participation in a semi-structured interview and for permission for data linkage to the observational cohort study.

Survey data will be analysed using descriptive and inferential statistics. Descriptive statistics with 95% CIs will be reported for the total sample (by planned mode of cervical ripening—home or hospital, by actual mode (as some women who plan one mode may in practice have a different mode) and by study site). We will examine whether there are statistically significant differences in the primary outcome of sense of control (labour agentry) and by psychosocial outcome of postnatal psychological well-being score (WEMWBS) between women with home cervical ripening and women with in-hospital ripening. The covariates will include the reason for IOL, gestational age, maternal age, parity, sociodemographic status and ethnic group.

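### The per-protocol sensitivity analysis selects on discharge home after ripening has started, in the home group only, so its bias is uncontrolled and its direction unknown

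*Protocol article*

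**What the plan says.** Under Exposure and outcomes, the groups are set by intention at the outset: "The exposure group will be women who, at the start of the cervical ripening process, plan to have home cervical ripening". The other group is drawn from different hospitals: "The comparator group will be women who planned to have in-hospital cervical ripening from maternity units not offering home cervical ripening". The stated reason is that, at units offering both settings, "the risk of complications in the babies of women having home cervical ripening (lower risk pregnancies) is inherently different" from that of babies whose mothers ripen in hospital.

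Under Statistical analysis, three sensitivity analyses are proposed. The second is a "per protocol analysis (women who actually are discharged home after commencing cervical ripening"). No restriction of the comparator is described.

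The Questionnaire-based survey section accepts that "some women who plan one mode may in practice have a different mode". The article does not say how many women planning home ripening are expected to stay in, why, or what their NNU risk is.

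The benchmark for size comes from the same article: "a non-inferiority design was chosen with a non-inferiority margin of 4" percentage points, with an "estimated 6% NNU admission rate" in the Sample size section.

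**The concern.** The main comparison is sound on this point because it classifies women by their plan at the start of ripening. The per-protocol set replaces that with an event that occurs later. A woman who planned home ripening but stayed in after insertion leaves the home group. A woman with the same course in a hospital-only unit stays in the comparator, because no discharge decision exists there.

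The matching model named in the article uses variables such as age, Bishop's score, previous vaginal birth, comorbidities and hospital-level factors. These are known before or at the start of ripening, so they cannot by themselves balance a selection that depends on what happens after insertion. The comparator from hospital-only units was chosen to avoid comparing groups sorted by risk. A one-sided discharge filter can bring back sorting of that kind at a later stage.

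Readers of a non-inferiority study often take a per-protocol result as a check against dilution. If it agrees with the main analysis, they may be reassured by an agreement that selection has partly produced.

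**Working it through.** **1. The plan's own figures.** Inputs from the Sample size section: 6% in both groups, a 4-point margin, 160 women in each of 12 sites per arm, "at 90% power, 2.5% one-sided alpha and an estimated ICC of 0.01".

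- Unclustered size per arm: (1.960 + 1.282)² × 2 × 0.06 × 0.94 / 0.04² = 741.
- Design effect: 1 + (160 − 1) × 0.01 = 2.59, and 741 × 2.59 = 1919 (stated: 1920).
- Overall: 1920 × 2 / 0.5 / 0.9 = 8533 (stated: 8533).

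The sample size reproduces and is not affected by this point.

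**2. Selection alone.** Two quantities are assumed because the article gives neither: f, the share of planned-home women kept in, and RR, their NNU risk relative to discharged women. The 50% in the Sample size section is uptake among eligible women, not f. With no true effect of setting and 6% overall:

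rate in discharged women = 6% / (1 − f + f × RR)

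| f | RR | Rate in discharged women | Shift (points) |
|---|---|---|---|
| 10% | 0.5 | 6 / 0.95 = 6.3% | +0.3 |
| 10% | 1 | 6 / 1.00 = 6.0% | 0 |
| 10% | 1.5 | 6 / 1.05 = 5.7% | −0.3 |
| 10% | 2 | 6 / 1.10 = 5.45% | −0.55 |
| 10% | 3 | 6 / 1.20 = 5.0% | −1.0 |
| 20% | 0.5 | 6 / 0.90 = 6.7% | +0.7 |
| 20% | 1 | 6 / 1.00 = 6.0% | 0 |
| 20% | 1.5 | 6 / 1.10 = 5.45% | −0.55 |
| 20% | 2 | 6 / 1.20 = 5.0% | −1.0 |
| 20% | 3 | 6 / 1.40 = 4.3% | −1.7 |

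For RR from 1 to 3 the shift is 0 to 1.7 points towards non-inferiority, at most 1.7 / 4 = 43% of the margin. Below RR 1 it goes the other way.

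**3. Selection and dilution together.** Suppose home ripening adds 4 points of risk, but only in women who actually go home, and f = 20%. RR now describes the women's risk apart from that added harm.

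- Planned-setting difference: 0.8 × 4 = 3.2 points, whatever the RR.
- Per-protocol difference: rate in discharged women from step 2, plus 4, minus 6.

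| RR | Per-protocol difference | Against the planned-setting 3.2 |
|---|---|---|
| 1 | 6.0 + 4 − 6 = 4.0 | less favourable to home |
| 1.5 | 5.45 + 4 − 6 = 3.45 | less favourable to home |
| 2 | 5.0 + 4 − 6 = 3.0 | more favourable to home |
| 3 | 4.3 + 4 − 6 = 2.3 | more favourable to home |

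The two analyses agree when the rate in discharged women is 5.2%, that is when 1 + 0.2 × (RR − 1) = 6 / 5.2, which gives RR of about 1.8. Below that, removing dilution outweighs selection; above it, selection wins. The per-protocol figure understates the true 4 points in discharged women whenever RR exceeds 1.

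**The case against.** A reader might infer that this analysis is biased towards non-inferiority as a matter of course. The documents do not support that. It requires women kept in to have higher NNU risk, and no section gives their number, reasons or risk. The lower-risk remark under Exposure and outcomes concerns who has home ripening at units offering both settings, not who is held back after insertion. It makes an RR above 1 plausible without establishing it. Step 3 also shows that, at a modest RR, the per-protocol result is less favourable to home than the planned-setting one. This part of the objection stands in full.

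Three further points have weight. This is one of three proposed sensitivity analyses; the principal analysis uses planned setting and is untouched. The article never says the per-protocol result will support the non-inferiority claim. The comparator is not wholly unselected, since it meets the same eligibility criteria and enters the matching. These points limit the importance of the problem but do not remove it.

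It can also be said that the detail belongs in the statistical analysis plan, which the article promises and which is not shown. That would answer a complaint about something left out. Here, however, the article states the defining criterion, and women in hospital-only units can neither meet nor fail it. That the comparator loses nobody is an inference, but it follows from the two definitions.

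**Conclusion.** The per-protocol set is defined by an event after exposure begins that can occur in one group only, and baseline matching does not by itself repair this. On the stated assumptions (10–20% kept in, RR 1 to 3), selection alone moves the home rate by 0 to 1.7 points against a 4-point margin. It moves in the opposite direction if RR is below 1. Once the removal of dilution is counted, the net direction relative to the planned-setting analysis is uncertain: with 20% kept in, it changes sign at an RR of about 1.8. These are illustrations, since f and RR are not in the documents. The supported conclusion is that the analysis, as defined, cannot be relied on as a conservative check. A conclusion that it must favour home ripening, or that the main comparison is compromised, is not supported. The point merits a change of wording in the analysis plan.

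**What to change.** Keep the planned-setting analysis as the basis for the non-inferiority conclusion, and say so. Then redefine the per-protocol analysis in one of these ways:

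1. Where event times are recorded, apply the same post-insertion landmark and the same exclusions to both groups.
2. Alternatively, weight discharged women by the inverse probability of discharge, using recorded baseline and post-insertion factors. This fails for any finding that always prevents discharge, because no discharged woman can then represent those kept in.
3. If neither is feasible, report the discharged-only analysis as descriptive, with the share kept in and their NNU rate, and state that it cannot on its own support non-inferiority.

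Feasibility of the first two must be checked. The Data sources section says antenatal events will be held as relative times, but it does not confirm timed records of abnormal cardiotocographs, membrane rupture or hyperstimulation.

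The cost is analysis-plan wording, with no extra recruitment. Under the first option some comparator women are lost from this one analysis; under the second its precision falls slightly.
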